### Interventions

#### Online Training

REsOluTioN was hosted on the Totara learning management system (version 12) by the Learning and Development (LD) information technology team of the participating NHS trust. A simple layout with clear instructions and prominent widgets to navigate the training pages will be used (Multimedia Appendices 1-3). More details about this are provided below.

##### Structure

REsOluTioN adopts a blended learning approach of asynchronous learning and synchronous sessions delivered in real time. The landing page includes a brief description about the training, module topics, library of learning materials, and a short welcome and introduction video by the study’s chief investigator.

Over a 4-week period, participants will be required to attend four facilitated online large group sessions on four module topics lasting up to 120 minutes in duration. Prior to each session, there will be 30 minutes of independent asynchronous preparatory activities. Additionally, they will attend online mentorship meetings in small groups; the mentors will all hold senior nursing positions at the participating trust. Mentor meetings will be conducted for 30 and 60 minutes twice weekly, at flexible times, over the 4-week training period.

##### Preparatory Activities

Prior to each large-group facilitated session, participants will be expected to complete some recommended readings on the module topic such as journal articles and reports, and tasks for further discussion during the sessions such as preparing responses to questions (related to module topics) such as “What does emotional intelligence mean to you and why it is important in your role?” and “What are your three main qualities of self-confidence?” The list of prereadings and tasks to be completed will be made available to participants in advance on the REsOluTioN online training page.

##### Large Group-Facilitated Sessions

Facilitated sessions will be scheduled in advance, and session dates and timings will be shared with those enrolled in each cohort. The facilitated session topics cover building hardiness and maintaining a positive outlook, intellectual flexibility and emotional intelligence, reflective and critical thinking, and achieving life balance and enabling spirituality. Experienced nurses and other multidisciplinary health care staff in senior clinical and academic positions within the local region will deliver the sessions. An outline of the content and objectives for each module is presented in Table 1.

**Table 1 table1:** Outline of REsOluTioN training.

Components of REsOluTioN^a^	Content	Objectives
Mentorship sessions: establishing positive nurturing relationships and network	Nurturing personal relationships Relationships that encourage and motivate Crucial conversations for health care work	Focus on protective aspects of positive relationships and networks on the effects of workplace adversity
Module 1: building hardiness and maintaining a positive outlook	Defining positive outlook and personal hardiness What is known about workplace hardiness? Strategies for success: prioritizing activities in time-pressured environments, learned optimism, assertive communication An authentic life Self-esteem Self-awareness: past, present, future	Identify the elements of a positive outlook and personality hardiness related to nursing Demonstrate benefits of a positive outlook and developing hardiness for job satisfaction, health, and well-being Formulate individual strategies for improving and maintaining a positive outlook and hardiness
Module 2: IF^b^ and EI^c^	IF: definitions and characteristics Links to nursing research and resilience Dimensions of EI Emotional labor Strategies for success: expand your thinking, creative thinking, self-monitoring, expressing emotion creatively	Define principles of IF and EI Define significant existing research findings regarding IF and EI as they relate to nursing Evaluate advantages of applying elements of IF and EI to nursing practice Reflect on strategies to assist creative/critical thinking
Module 3: reflective and critical thinking	What is reflection? Making meaning of experience Moving from description to reflection Understanding reflection Therapeutic use of self Reflective awareness Reflective action	Identify importance of therapeutic use of self and reflection in expert practice Demonstrate understanding of the benefits of the reflective process to nursing practice and its underlying knowledge, influences, and motivations Define a model of reflection shown to increase critical thinking skills and develop reflexive practice Analyze individual strategies to creatively access and explore the reflection process
Module 4: achieving life balance and enabling spirituality	Work/life balance: What is balance? Why is it so hard? Envisioning work/life balance Historical, gender, and power contexts Assumptions about “juggling” Strategies for success: being comfortable doing less; adding new things to life Enabling spirituality: definition Spirituality and nursing care, health Women, spirituality, and communities	Define the importance of an awareness of work/life balance for health and well-being Demonstrate strategies for improving work/life balance Formulate historical/political background of women’s roles in caring and other work Explore some aspects of spiritually responsive nursing care available to them Explore personal perspectives on individual spirituality and its relationship to contemporary lifestyles
All modules (cross-cutting): moving forward and planning for the future	The reflective process Reflection and expert practice Strategies for success: thinking critically, reflection circuit, exhibition and participant presentations, planning for the future (goal setting)	Identify features of a resilient person and relate them to individual experiences Formulate strategies for continuation and permanency of resilient beliefs and behaviors Demonstrate an understanding of the ongoing process of resilience and the protective benefits of committing to the long-term maintenance of personal well-being

^a^REsOluTioN: Resilience Enhancement Online Training for Nurses.

^b^IF: intellectual flexibility.

^c^EI: emotional intelligence.

##### Mentor Meetings

Mentor meetings will be designed to be rewarding and valuable components of the REsOluTioN package. A mentor pool will be established by inviting around 15 experienced registered nurses from the participating trust to contribute to the study as mentors. Mentors will be registered nurses working at a Band 7 level or above. Generally, nurses working at these levels require appropriate leadership or management skills and have widespread experience of the pressures and challenges of working within the NHS. Mentors will be expected to commit to two weekly meetings with mentees for 4 weeks per cohort (mentors will be able to sign up for one or more cohorts). The mentor meetings will aim to support the mentees while they are training and to facilitate discussion relating to a wide range of topics, including but not limited to the topics covered during the facilitated sessions; the course of the discussion will be led by the mentees. The roles and expectations, issues of accountability, and key goals of the mentoring partnership will also be covered. However, this will not be a formal mentorship relationship and as such no predefined structure or mentoring plans are required.

Two separate documents with frequently asked questions to inform mentors and mentees about the structure and conduct of mentor meetings will be developed. Mentors and mentees will not be expected to maintain additional contact between the weekly meetings though they can choose to do so if they feel it would add benefit.

##### Delivery of Content

All facilitated sessions and mentor meetings will be delivered online within the parameters of confidentiality via Teams (Microsoft Corporation). Meeting links and reminders will be sent to the participants through the LD platform. Content delivery and user engagement of REsOluTioN will be in the form of text materials, illustrations, PowerPoint (Microsoft Corporation) presentations, explanatory videos, case examples, and additional reference documents such as peer-reviewed journal articles and published guidance. The facilitated sessions will also include discussions, small group work, and breakout activities. A separate YouTube account will be created for the trial, and all REsOluTioN-related videos will be made accessible only to the trial participants.

##### Time Commitment

At the end of 4 weeks, participants randomized to REsOluTioN will have completed 10 hours of structured content (2 hours of self-learning activities and 8 hours of scheduled facilitated sessions) in addition to 4-8 hours of flexible mentor meetings.

#### Control Arm

Nurses randomized to the control arm will be allocated to a wait list for 6 weeks. When they have completed the online poststudy surveys at the end of the sixth week, they will be provided access to REsOluTioN study materials.

### Outcomes

#### Participant Engagement With the Trial

Data will be collected on the number of registered nurses who expressed an interest, enrolled, were randomized, or withdrew from the study to estimate the recruitment rate and nurses’ engagement with the trial.

#### Training Outcomes

##### Acceptability of REsOluTioN

Data will be collected on the number of registered nurses who complete REsOluTioN, discontinued in between, and did not complete the posttraining survey to estimate the acceptability of REsOluTioN.

##### Resilience and Psychological Well-being

The validated Brief Resilience Scale (BRS) [24] and Warwick-Edinburgh Mental Wellbeing Scale (WEMWBS) [25] will be used to measure changes in resilience, psychological health, and well-being over time. The BRS is a brief measure of an individual’s ability to “bounce back” and has been found to have good psychometric properties compared to measures of resilience [24]. The WEMWBS has been widely used in clinical settings to measure the effects of interventions to improve well-being and can provide an indicator of resilience [25].

##### Perceived Usefulness of REsOluTioN

At baseline, the following survey data will be collected from those randomized to REsOluTioN: understanding of resilience, what they hope to gain from it, levels of perceived resilience, confidence, workplace satisfaction, and peer support.

At 6 weeks (2 weeks post training), participants’ perceived usefulness of REsOluTioN and their perceived levels of personal resilience, self-confidence, belief in own ability to provide quality patient care, relationship with work colleagues, communication skills with colleagues, outlook toward clinical practice, understanding of resilience, and feedback on REsOluTioN will be determined via an online survey.

### Data Collection Methods

Participants who expressed interest to participate in the trial will be provided a prestudy survey to provide online consent and demographic information (type of work clinical setting, banding, ethnicity, age, years of experience) before the start of each cohort and 2 weeks post cohort completion (sixth week). Surveys will be hosted on the Qualtrics online survey platform.

The surveys will contain both closed- and open-ended questions and the validated BRS [24] and WEMWBS [25]. Resilience and mental well-being scales will be completed by participants in the control and REsOluTioN arms. The closed survey questions will be completed by all participants and will take a 1 to 5 Likert-style format, with responses ranging from “not important at all” to “extremely important” or “not useful at all” and “extremely useful.” The open-ended survey questions will only be completed by REsOluTioN arm participants and will seek feedback relating to what they enjoyed the most about the training and whether any specific modules were particularly helpful.

Following completion of the postsurveys, those randomized to REsOluTioN will receive a training certificate for 10 continuing professional development (CPD) hours and those in the wait list control group will be given access to REsOluTioN materials and the 10 hours CPD training certificate.

### Data Management

Online informed consent will be obtained from all participants. All data will be stored securely in line with the university’s (study sponsor) policies for data management and storage, and in line with General Data Protection Regulation requirements.

Direct access to source data will be made only to the designated members of the study team as authorized by the chief investigator. All participant-identifiable information will be removed and anonymized using study identification codes. Electronic deidentified data will be stored and backed-up in password-protected Excel (Microsoft Corporation) spreadsheets in a secured drive accessible by the study team only. Data will be retained for 5 years after the completion of the trial.

### Statistical Methods

Demographic characteristics of the study participants will be descriptively summarized. The proportion of participants who enrolled, completed the study, provided follow-up data, or discontinued the study, and those responding to each category on the Likert-type closed questions in the survey will be reported. Pre- and postsurveys on resilience and psychological well-being will be presented as means (SDs) or medians (IQRs) depending on the normality as per Shapiro-Wilk test. The differences in resilience and psychological well-being within each arm and between arms at 6 weeks will be assessed using analysis of variance. A significance level of 0.05 will be considered. All analysis will be undertaken in SPSS statistics software, version 22.0 (IBM Corp) [26].

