**Objective:**

This study aims to compare levels of resilience, psychological health, and well-being in nurses before and after the online resilience training compared to a wait list control group. It will also explore participants’ engagement with the trial and their acceptability of the online training.

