**Methods:**

This is a two-arm, parallel, randomized controlled trial with a 6-week follow-up period. Up to 100 registered nonagency nurses working at a National Health Service hospital trust in South England will be recruited. Four cohorts will run, and participants will be randomized into a wait list control group or to REsOluTioN. Pre- and postonline surveys will collect study outcome measure data. In the REsOluTioN arm, data will be collected on the perceived usefulness of the online training via an online survey. Institutional and health research authority approvals have been obtained.

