### Sample Size

Given the study objective to afford a preliminary comparison of training outcomes, as well as funding constraints and the pressures imposed by COVID-19, we propose to recruit a minimum of 60 and up to 100 participants. We aim to recruit participants over four cohorts with approximately 25 participants per cohort.

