### Allocation

After providing online consent, participants will be randomized to receive either the wait list control or REsOluTioN on a 1:1 ratio. An independent research staff not involved in the design and conduct of the trial will generate a computer-generated random number sequence. Allocation concealment will be upheld using sequentially numbered opaque-sealed envelopes that will be opened sequentially only after entering the name of each participant on the envelope. A research team member who is not involved in the delivery of REsOluTioN or data analysis will implement the group allocation and contact participants to inform them of their group allocation.

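### The between-arm test is an analysis of variance of 6-week scores with no baseline term, so precision available from the BRS and WEMWBS baselines is lost in a trial of 60 to 100 nurses

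*Protocol article*

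**What the plan says.** The Objective in the abstract is to compare resilience, psychological health and well-being "before and after the online resilience training compared to a wait list control group". The abstract's Methods paragraph states that "Pre- and postonline surveys will collect study outcome measure data", and Data Collection Methods confirms that "Resilience and mental well-being scales will be completed by participants in the control and REsOluTioN arms". The Blinding section places the surveys at the start of the study and after 6 weeks. A baseline and a 6-week value of each scale are therefore planned for both arms.

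Statistical Methods then specifies the inference in one sentence: "The differences in resilience and psychological well-being within each arm and between arms at 6 weeks will be assessed using analysis of variance". It adds that "A significance level of 0.05 will be considered" and names the software. It does not mention a baseline covariate, a change score, a repeated-measures model or an arm-by-time term.

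Under Sample Size, "we propose to recruit a minimum of 60 and up to 100 participants". The reasons given are the preliminary nature of the comparison, funding and COVID-19 pressures. No power, effect size or standard deviation is stated.

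**The concern.** On its plain reading, the sentence uses baseline scores only for the within-arm differences, while the randomized comparison rests on 6-week scores alone. A nurse's own starting score is usually the strongest available predictor of her or his later score on the same scale. Leaving it out keeps variation between nurses in the error term that the model could have removed.

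With 30 to 50 per arm, a visible chance difference in baseline scores is also quite likely. A post-only comparison carries a fraction r of that difference (in SD units) into the estimated effect.

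The between-arm comparison of these scales is the first objective listed in the Introduction, and the Discussion makes a larger national trial conditional on what it shows. An unnecessarily wide interval weakens that decision.

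**Working it through.** The article contains no power calculation to reproduce, so the check compares the precision of the possible analyses of the same data.

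**Inputs from the protocol article**
- Total sample 60 to 100 (Sample Size), allocated 1:1 (Allocation), so 30 to 50 per arm.
- Significance level 0.05 (Statistical Methods). Two-sided testing is assumed, because sidedness is not stated.

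**Inputs assumed, because the documents do not give them**
- Correlation r between baseline and 6-week score: 0.6, with a range of 0.4 to 0.8.
- True difference of 0.5 SD, used for illustration.
- Equal SDs at the two times, and no dropout. Dropout would lower every power figure.

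**Step 1. Variance of the arm difference, relative to the post-only analysis**
- Post-only ANOVA: 1.
- Change score, which is the same test as arm-by-time in a two-occasion repeated-measures ANOVA: 2(1 − r).
- ANCOVA on baseline: 1 − r².

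The difference between the last two is 2(1 − r) − (1 − r²) = (1 − r)², which is positive for every r below 1. ANCOVA is therefore always at least as precise as the change score.

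| r | Post-only | Change score | ANCOVA | 60 nurses under ANCOVA equal, post-only |
|---|---|---|---|---|
| 0.4 | 1 | 1.20 | 0.84 | 60/0.84 = 71 |
| 0.6 | 1 | 0.80 | 0.64 | 60/0.64 = 94 |
| 0.8 | 1 | 0.40 | 0.36 | 60/0.36 = 167 |

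The standard error falls by 1 − √(1 − r²), which is 8%, 20% and 40% at r = 0.4, 0.6 and 0.8.

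**Step 2. Power for a 0.5 SD difference**

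This uses the noncentral t distribution with 2n − 2 degrees of freedom and noncentrality 0.5 / √(f × 2/n), where f is the variance factor from step 1 and n the number per arm.

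| n per arm | r | Post-only | Change score | ANCOVA |
|---|---|---|---|---|
| 30 | 0.4 | 48% | 41% | 55% |
| 30 | 0.6 | 48% | 57% | 66% |
| 30 | 0.8 | 48% | 85% | 89% |
| 50 | 0.4 | 70% | 62% | 77% |
| 50 | 0.6 | 70% | 79% | 87% |
| 50 | 0.8 | 70% | 97% | 98% |

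Removing four further degrees of freedom (one for baseline, three for cohort) changes the ANCOVA figures by about 0.1 percentage point.

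**Step 3. Chance imbalance at baseline**

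The baseline difference between arms has standard error √(2/n) SD: 0.258 at n = 30 and 0.200 at n = 50. The probability that it exceeds 0.25 SD in either direction is 2[1 − Φ(0.25/0.258)] = 33% and 2[1 − Φ(0.25/0.200)] = 21%. At r = 0.6, a gap of 0.25 SD would shift the post-only estimate by 0.6 × 0.25 = 0.15 SD. ANCOVA removes that shift.

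**The case against.** The strongest objection is to the reading. One method is named for differences both within and between arms, and a within-arm difference needs the baseline, so the sentence could loosely describe a repeated-measures ANOVA. If so, the baseline is not ignored and the loss at r = 0.6 is smaller: 57% against 66% power at 30 per arm, and 79% against 87% at 50 per arm, with 60 nurses under ANCOVA worth 60 × 0.80/0.64 = 75 rather than 94. This is fair as to size. It does not remove the point, because the arm-by-time test loses to ANCOVA at every r below 1 and is worse than post-only when r is below 0.5. The arm main effect in such a model averages the pre and post scores and does not answer the question.

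Second, an unadjusted comparison of randomized arms is unbiased and holds its type I error, and its standard error already allows for chance imbalance. That stands. The fault is lost precision, and the imbalance is one way of seeing it rather than a separate bias.

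Third, this is a pilot with no claim to power, and the correlation and effect size are assumptions. Both are true, and at low r the gain is modest (48% to 55% at r = 0.4 with 30 per arm). But a test at 0.05 is planned for the first listed objective, the sample is limited by circumstance, and the added precision costs nothing.

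Fourth, covariates are often left to an analysis plan. Here, however, the article states the method and the time point, so the criticism is of a stated choice and not of missing detail.

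**Conclusion.** The concern holds. As written, the between-arm comparison makes no use of baseline scores planned for every participant, and gives up a fraction r² of the error variance relative to ANCOVA: 36% at r = 0.6, with a range of 16% to 64% for r from 0.4 to 0.8. The direction of the loss does not depend on which reading of the sentence is taken. Its size depends on r, and the power figures also depend on the illustrative 0.5 SD effect and on full follow-up. The planned test is not invalid. This is a worthwhile efficiency correction that should be made.

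**What to change.** In Statistical Methods, replace the between-arm ANOVA with a linear model (ANCOVA), fitted separately for BRS and WEMWBS: 6-week score on arm, the baseline score of the same scale, and cohort. Report the adjusted mean difference with its 95% confidence interval. Baseline adjustment is the essential part. The cohort term is secondary, but reasonable because recruitment runs over four cohorts.

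The cost is one sentence, one degree of freedom for baseline and three for cohort, and no new data. The article says the trial has finished, so the change should be recorded as a dated, disclosed amendment. Failing that, ANCOVA should be reported as a supporting analysis beside the analysis originally planned.

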Recent literature has recommended that resilience-building initiatives, including mentorship programs outside of nurses’ immediate workplace settings, are incorporated into nursing education, as well as specific self-development strategies to help enhance personal resilience [15]. Resilience programs have been found to build and enhance nurses’ resilience and can also support recruitment and retention for health care workers [16]. This has been evidenced in a number of recent workplace resilience enhancement interventions within nursing [17-22].

As a result of the need for targeted resilience enhancement interventions within the nursing setting, a UK-based resilience enhancement program was developed [22,23]. A detailed description of the theoretical background of the program is available elsewhere [22]. This face-to-face program targets four core components to improve the ability of the nurses to bounce back from day-to-day problems and to remain resilient in the workplace: workplace hardiness, emotional intelligence, critical thinking, and achieving life balance and enabling spirituality. These components were informed by a 2014 integrative review [15] that reported difficult workplace situations, feelings of emptiness, and a diminishing sense of inner balance as main contributing factors for resilience in nurses. Various strategies such as reflecting on emotions, interactions and guidance from peers and mentors, and skills to develop work-life balance and toughening up are shown to be helpful in building resilience.

The program consisted of six sessions with nurses that covered topics including building hardiness, maintaining a positive outlook, achieving work-life balance, reflective and critical thinking, and enabling spirituality [22,23]. In addition, one-to-one mentor sessions were provided over a 12-week period; senior nurse leaders within the participating trust took on these mentorship roles [23]. The face-to-face program was evaluated using pre- and postsurveys and interviews with nurses. Findings showed that nurses’ resilience levels were significantly higher after the training, with reported positive impacts on personal resilience, self-awareness, confidence, well-being, and professional and team-working relationships [22]. As a result, a wider rollout of the training was proposed. However, this planned rollout was disrupted by the onset of the COVID-19 pandemic due to social-distancing measures, making the face-to-face training untenable.

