Due to the restrictions imposed by COVID-19, the face-to-face training program [22,23] was adapted and transformed to online training as a means of increasing accessibility for all nurses who were no longer able to attend face-to-face training. The online training was also informed by a recent systematic review examining the effectiveness of online interventions to enhance resilience in health care professionals ([name], unpublished data, 2022) and focus groups with nurses to gather information on what they felt should be key features of an online resilience training program. An online format was felt necessary due to its potential to be rolled out widely to all nurses working in health care settings due to ease of accessibility, flexible access, and a decreased need for other resources such as physical space and in-person facilitation. The online resilience training, entitled Resilience Enhancement Online Training for Nurses (REsOluTioN), is relevant in the COVID-19 climate, where consideration about how to optimize the experiences of the nursing workforce and the resulting impacts on patient care are urgently needed.

In light of the above, the randomized controlled trial described in this paper aims to pilot REsOluTioN, an online resilience training for nurses working during COVID-19. Specific study objectives are:

To compare levels of resilience, psychological health, and well-being in nurses who complete REsOluTioN with nurses who do not (control arm)To explore participant engagement with the trial and acceptability of REsOluTioNTo collect feedback on various components of REsOluTioN

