### Blinding

Participants will not be blinded to their group allocation and will complete self-reported online surveys at the start of the study and after 6 weeks. It is not possible to blind the team member who undertakes the allocation assignment; however, other research team members who analyze the pre-post survey responses will be blinded to treatment allocation.

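### Within-arm pre-post tests share the 0.05 level with the between-arm comparison, and nothing says which one supports an effect claim

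*Protocol article*

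**What the plan says.** The Statistical Methods section of the protocol article plans that differences in resilience and psychological well-being "within each arm and between arms at 6 weeks will be assessed using analysis of variance". It then adds: "A significance level of 0.05 will be considered". One sentence, one method and one level cover both kinds of test. The within-arm tests are not called descriptive, and the between-arm test is not named as the one that decides.

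Other parts of the article bear on how the tests will be read:

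- The first objective (end of the Introduction) compares nurses who complete the training with a control arm, so it is a between-arm objective.
- Two scales are used, and neither is named as primary: "The validated Brief Resilience Scale (BRS) [24] and Warwick-Edinburgh Mental Wellbeing Scale (WEMWBS) [25] will be used to measure changes in resilience" (Resilience and Psychological Well-being).
- Participants are not blinded and "will complete self-reported online surveys at the start of the study and after 6 weeks" (Blinding).
- The Discussion says that if the findings show the program to be effective, it will go forward to a larger national randomized trial. It does not say which test would show this.
- The Introduction reports that, in the earlier face-to-face program, "resilience levels were significantly higher after the training". That was a pre-post evaluation, and a wider rollout was proposed as a result.

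**The concern.** A pre-post test inside one arm does not use the wait-list arm. The change it measures is any training effect plus whatever happens to both arms over the six weeks. That can include regression to the mean, answering the same self-report scales a second time, and changing pandemic pressure (the trial ran from August 2021 to May 2022). The control arm is there to remove these.

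When both arms are tested separately at 0.05, a likely pair of results is a significant improvement in one arm and a non-significant change in the other. It is easy to read this as an effect of the training. It is not a test of the difference between arms, because two arms with the same true change can fall on either side of the 0.05 line by chance. If the claim of effectiveness rested on that pattern, the randomized trial would add little to the earlier pre-post evaluation, and the decision on a national trial would rest on evidence that ignores the control group.

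**Working it through.** The article gives no power, effect size, SD or expected change, so there is no figure of its own to reproduce. The question is how often the misleading pattern appears when the training does nothing.

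**Inputs from the article**

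- Level 0.05 (Statistical Methods). Sidedness is not stated; two-sided is assumed.
- Size: "we propose to recruit a minimum of 60 and up to 100 participants" (Sample Size).
- Ratio: "participants will be randomized to receive either the wait list control or REsOluTioN on a 1:1 ratio" (Allocation). This gives 60/2 = 30 to 100/2 = 50 per arm.

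**Assumptions, not in the documents**

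- No training effect. Both arms improve by the same amount, d, in units of the SD of the score.
- Pre-post correlation r = 0.6, no dropout, and a paired test within each arm (with two time points this equals a repeated-measures ANOVA).

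**Formulae**

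1. The SD of the change is √(2(1 − r)) = √0.8 = 0.894 score SDs, so the standardized change is d/0.894.
2. The probability p that one arm's test is significant comes from the noncentral t distribution with n − 1 degrees of freedom and noncentrality (d/0.894)√n. Let u be the part of p in the direction of improvement.
3. The arms are independent, so P(REsOluTioN significantly improved, control not significant) = u(1 − p). When almost all significant results are improvements this is close to p(1 − p), which cannot exceed 0.5 × 0.5 = 0.25.

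**Worked case:** d = 0.3, n = 40. The standardized change is 0.3/0.894 = 0.335 and p = 0.543. The pattern has probability 0.543 × 0.457 = 0.248.

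**Range, per outcome**

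| Shared improvement d | 30 per arm | 40 per arm | 50 per arm |
|---|---|---|---|
| 0 | 2.4% | 2.4% | 2.4% |
| 0.1 SD | 7.8% | 9.1% | 10.4% |
| 0.2 SD | 17.1% | 20.2% | 22.5% |
| 0.3 SD | 24.5% | 24.8% | 23.0% |
| 0.4 SD | 22.5% | 16.7% | 11.1% |
| 0.6 SD | 5.3% | 1.5% | 0.4% |

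The first row is 0.025 × 0.95 = 0.024. The frequency rises with the shared change, peaks near the 25% ceiling when each arm has about an even chance of significance, and falls again when both arms are nearly always significant.

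**Comparison with the between-arm test.** In a simulation of 20,000 trials per setting (30 or 50 per arm, shared change from 0 to 0.5 SDs of the change score), a between-arm t test on change was significant in 4.7% to 5.1% of trials per outcome whatever the shared change. About half of these, 2.5%, favour the training. Among the no-effect trials that showed the misleading pattern, 66% to 91% had a non-significant between-arm test.

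**Two scales.** With an assumed correlation of 0.5 between the changes on the two scales, the same simulation found the pattern on at least one scale in about 4% of trials with no shared change and in up to about 39% otherwise.

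**The case against.** The strongest reply is that the correct comparison is already planned, in the same sentence, and matches the stated objective. The article is also a condensed account of a pilot. A positive finding would lead to a larger randomized trial, where a misreading could be put right. This stands, and it lowers the severity. It does not remove the point: the article itself commits to within-arm tests at 0.05, and nothing in it puts them below the between-arm test.

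A reader might infer that the trial will declare the training effective from a significant change in one arm and not in the other. The article states no such rule. The risk lies in how the results may be interpreted. The account of the face-to-face program shows how a pre-post result was used before, but it does not show how this trial will be read.

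A reader might also infer that the pattern is common whenever the training has no effect. It is not. With no shared change it is no more frequent than a false-positive between-arm result in favour of training, and the 25% figure is the ceiling.

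Finally, a reader might infer that the within-arm ANOVA would treat a nurse's two scores as independent. The article says only analysis of variance, which fits a repeated-measures model equally well, so that criticism has no basis in the text. It would also undercut the frequencies above: at 40 per arm and r = 0.6, an unpaired analysis shows the pattern in about 14% of trials for a 0.3 SD shared change, against 25% for the paired one.

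**Conclusion.** The point holds as a gap in how the analysis is fixed. Within-arm significance tests are planned on the same footing as the between-arm comparison, and the article does not say which supports an effect claim.

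The size is conditional. About 8% to 25% of no-effect trials per outcome would show REsOluTioN significantly improved and control not, if both arms improve by 0.1 to 0.4 SD; the corresponding error of a valid between-arm test is 2.5%. This rests on paired two-sided tests, r = 0.6, 30 to 50 per arm and no dropout. The size of any shared change cannot be taken from the documents. If it is zero or large, the pattern is rare.

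Because the trial is a pilot and already plans the right comparison, this should be fixed but is not a fatal error.

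**What to change.** Replace the within-arm tests with description: pre score, post score and mean change for each arm and scale, without p-values. State that every effectiveness statement, including the one that decides on a larger trial, rests on the between-arm difference at 6 weeks adjusted for the baseline score (ANCOVA), with its 95% CI.

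Both scales are collected from both arms before and after, so no new data are needed. The cost is a line or two of wording and the loss of within-arm p-values. The article says that the trial has finished and that its findings are still to be presented, so the change can be made in the analysis and the report. It should be dated and declared as made after data collection.
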